## Methods

### Study Design

This study uses an intensive longitudinal burst design to periodically deliver EMA surveys over 6 months of maintenance chemotherapy that includes daily prescribed oral 6-MP to AYAs with acute lymphoblastic leukemia or lymphoma and their caregivers. Within the observational EMA study is an embedded microrandomized trial—an experimental design for optimizing mHealth interventions [29]—that randomizes engagement components within person and across EMAs as an early check on their efficacy before incorporating and piloting in a later JITAI.

At baseline, the enrolled AYAs and their caregivers will complete a demographic survey; brief screening measure of executive functioning; and assessment of COVID-19 exposure, impact, and distress [44] via REDCap (Research Electronic Data Capture; Vanderbilt University). Using the ADAPTS app, each participant will then receive EMA in *bursts* over the course of 6 months of maintenance therapy, capturing a time frame known to be associated with AYA 6-MP nonadherence and cancer relapse. In month 1 (28 days; ie, burst 1), EMA surveys will be sent once per day via the app to fully capture contextual processes during the month between follow-up medical appointments. To balance participant burden while also ensuring data are representative, in months 2-6, EMA surveys will be delivered once per day at the same time (6 PM), for one full week (2 weeks after the last maintenance appointment to approximate the midpoint between clinic visits when the AYA may have decreased adherence; for 35 days total), resulting in *bursts* of EMA data collection [45]. Burst designs such as this have been used to study other AYA health behaviors over a longer period [46]. Each AYA will receive a MEMS TrackCap (AARDEX Group), a validated electronic adherence monitor that was also used in the Children’s Oncology Group study, to measure daily 6-MP adherence across the entire study period.

EMA surveys are brief (<1 minute to complete) and assess intrapersonal contexts (eg, individual-level variables, such as nausea, fatigue, and positive or negative affect) and interpersonal contexts (eg, family and social environment variables, such as recent family interaction and location). Enrolled AYAs will complete 11 daily survey questions, and their caregivers will complete four survey questions (see Table 1 for a complete list of survey items).

**Table 1 table1:** Ecological momentary assessment (EMA) survey questions.

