**Intrapersonal contexts**							
	Physical symptoms	AYA^a^		How much pain are you currently experiencing? How much fatigue are you currently experiencing? How much nausea are you currently experiencing?		Three items assessing the intensity of current pain, fatigue, and nausea on a scale of 0 (not at all) to 4 (extremely); adapted from two adult oncology EMA studies [47,48]	
	Positive and negative effect	AYA and caregiver		How positive were you feeling (happy or joyful) just before you received this text message? How negative were you feeling (stressed, mad or angry, nervous or anxious, or sad) were you feeling just before you received this text message?		Two items assessing the degree of positive affect and negative affect on a scale of 0 (not at all) to 4 (extremely); adapted from a physical activity EMA study [49,50]	
	Adherence motivation	AYA		How motivated are you to take 6-MP^b^ today?		One item assessing motivation to take 6-MP on a scale of 0 (not motivated) to 4 (extremely motivated); adapted from EMA study of medication adherence in adults with HIV [51]	

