### Study App (ADAPTS)

The finalized version of ADAPTS delivers EMA surveys to the AYAs and their caregivers, as well as several engagement strategies (Figure 1). The app is available for both iPhone and Android users. Surveys are available between 6 PM and midnight. If the surveys are not completed by 8 PM, participants will receive a reminder. Automated engagement strategies will include the following: (1) pre-EMA nonmonetary engagement strategies (inspirational celebrity quotes and survey reminders; Multimedia Appendix 1 for a complete list of quotes); (2) post-EMA nonmonetary rewards (funny memes, altruistic messages, and a growing virtual environment from an aquarium to an ocean, tundra, and then a rainforest; Figure 2 and Multimedia Appendices 2 and 3 for complete lists of memes and altruistic messages); and (3) post-EMA small monetary rewards (US $2 for completing surveys on every first day of a new EMA cycle, then US $1 for every 3-day streak with 100% completion of surveys).

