### Microrandomization

Before the EMA survey being sent, participants will be randomized every day at 4 PM, with a probability of 0.5, to receive a push notification with an inspirational celebrity quote or to receive nothing (Figure 1). Consistent with the original SARA app, this incentive will be sent before the EMA survey is available to facilitate reciprocity; that is, to increase the likelihood that participants will *return the favor* by completing the survey when it is later available. After the EMA survey is completed, participants will be randomized with a 0.33 probability of receiving a funny meme (targeting extrinsic motivation), an altruistic message (targeting intrinsic motivation), or nothing. The other engagement strategies (ie, money and growing virtual environments) will not be randomized. The caregiver version of the app includes nonmonetary rewards (same growing virtual environment) and small monetary rewards (same compensation schedule) but does not include AYA-focused memes or quotes.

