### Primary Data Analyses

This data set will consist of 30 AYA-caregiver dyads×63 days=a maximum of 1890 daily observations. EMA predictors include data from AYAs, caregivers, or dyadic data from both reports (eg, agreement between AYAs and caregivers that they had a disagreement that day). Tables and graphs will be created to demonstrate how 6-MP adherence varies by individual (physical symptoms, mood, and motivation), family (family disagreements and problems with communication), and social-environmental factors (time of day, day of the week, month of the year, where AYAs were, and who they were with). Mixed effects models will be used through SAS PROC GLIMMIX (SAS Institute) to examine whether EMA of contextual factors predicted the binary daily 6-MP adherence outcome. Separate mixed effects models will be constructed for different predictors and include the predictor as the fixed effect and a random intercept for each participant to account for between-person variability. Mixed effects models may also include demographic and treatment covariates (eg, race, ethnicity, and time since cancer diagnosis) as fixed effects if they demonstrated a significant association with the outcome. We will decompose the between-subject and within-subject effects of EMA of contextual factors by creating two predictors from the original score: (1) the individual mean across all time points (between-subject predictor) and (2) the deviation of the daily score from the individual mean (within-subject predictor). Given the embedded engagement strategies, we expect minimal missing data, and mixed effects modeling will be able to use all available outcome data and provide valid inferences if missingness is at random. However, we will examine the amount and pattern of missing data, and if missing is suspected to be not at random, sensitivity analyses will be performed to assess the robustness of the primary analysis results. Significant findings will inform tailoring variables for future JITAIs (eg, tailor messages based on affect, motivation, and day of week).

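### The daily adherence models omit the quote randomized at 4 PM, two hours before AYA current-state ratings; adding it is a minor, nearly free safeguard

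*Protocol article*

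**What the plan says.** The Study Design section places an experiment inside the observational study: "Within the observational EMA study is an embedded microrandomized trial". Under Microrandomization, AYA "participants will be randomized every day at 4 PM, with a probability of 0.5, to receive a push notification with an inspirational celebrity quote" or nothing. The caregiver app "does not include AYA-focused memes or quotes".

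The survey comes after the quote. In the Study App section, "Surveys are available between 6 PM and midnight". Table 1 ties the affect items to the moment of the prompt ("How positive were you feeling (happy or joyful) just before you received this text message"), and the motivation item asks "How motivated are you to take 6-MP^b^ today". Pain, fatigue, nausea and loneliness are also current states, and location and company refer to the moment before the survey. The disagreement and communication items look back over 24 hours.

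Primary Data Analyses then specifies the adherence models: "Separate mixed effects models will be constructed for different predictors and include the predictor as the fixed effect and a random intercept for each participant". Each predictor is split into a person mean and a daily deviation from it. Demographic and treatment covariates may enter if they are significantly associated with the outcome; the examples are race, ethnicity and time since diagnosis. Quote assignment is not mentioned. The Secondary Outcome and Exploratory Analyses sections use the microrandomization for survey completion only, so no described analysis relates the quote to mood, motivation or adherence.

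**The concern.** The quote is a day-level input that the study itself generates, and it precedes the AYA's current-state ratings by at least two hours. It could be a common cause of predictor and outcome if an inspirational message lifts the rating and a notification from the study app separately cues the dose. Because it varies within person from day to day, any association it creates falls on the within-person coefficient. That coefficient carries the primary hypothesis about daily fluctuations. A random intercept, person-mean centring and person-level covariates all act between persons and leave it untouched.

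At stake is the choice of tailoring variables. The plan says significant findings will inform them and names affect and motivation as examples. Part of such a finding could come from the study's own prompts.

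**Working it through.** **The plan's own figures.** The maximum number of observations is 30 × 63 = 1890, as stated. With within-subject correlation 0.5, the effective sample size is 1890 / (1 + 62 × 0.5) = 1890 / 32 = 59.06, which matches the stated 59. The stated detectable odds ratio of 2.8 serves here only as a yardstick. A standard closed-form calculation with N = 59, 20% nonadherence, two-sided 0.05 and 80% power gives 2.49. That gap is a separate matter and nothing below depends on it.

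**Inputs.** From the protocol: quote probability 0.5, 30 AYAs, 63 days, about 20% missed doses. Assumed, because the documents give no values: the shift d of the rating in within-person SDs, the odds ratio of the quote for a missed dose by a route other than the rating, and a random-intercept SD of 1.5.

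**Size of the bias when the true context effect is null.** A 0/1 indicator with probability 0.5 has variance 0.25. The spurious within-person log odds ratio per SD is therefore approximately

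|bias| = 0.25 × d × |ln(OR)|.

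Dividing by 1 + 0.25d² refines this slightly and lowers it by at most 6% at d = 0.5.

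**False-positive rate.** Simulation of 30 × 63 days gives a within-person standard error of about 0.066. The approximate two-sided rate is Φ(−1.96 + bias/SE) + Φ(−1.96 − bias/SE).

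| d | OR for a miss | bias | bias/SE | approximate rate | simulated, planned model |
|---|---|---|---|---|---|
| 0.2 | 0.80 | 0.011 | 0.17 | 5.3% | 5.1%; 6.4% |
| 0.3 | 0.67 | 0.030 | 0.46 | 7.4% | 8.6%; 6.6% |
| 0.5 | 0.67 | 0.050 | 0.76 | 11.8% | 10.7–14.4%; 13.0% |
| 0.5 | 0.50 | 0.087 | 1.31 | 25.9% | 26%; 20.2% |

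The last column shows two sets of simulations, with 700–800 runs and 500 runs per scenario. With the quote indicator in the model, the rates were 3.3–6.3% and 5.2–6.6%.

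**Large-sample check.** This used 6,000 persons × 63 days with the person intercept supplied. The quote effect is coded here to act in the same direction as the rating.
- Null link, d = 0.5, quote OR 1.5: spurious OR 1.05, and 1.00 with the indicator.
- Null link, d = 0.5, quote OR 2.0: spurious OR 1.09, and 1.01 with the indicator.
- Quote moves only the rating, or only the dose: 0.99 and 1.00, so no bias from omission.
- True OR 1.5: 1.55 when omitted (d = 0.2, quote OR 1.5) and 1.62 (d = 0.5, quote OR 2.0). With the indicator these are 1.52 and 1.50.

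**The case against.** The strongest objection is that bias needs two effects at once, and the documents support neither. The quote must move the rating and also move the dose by another route. A reader might infer that any quote effect on mood and on the dose is misread as a natural link. That does not follow: if the quote lifts mood and mood changes dosing, the mood–adherence link is real. This part of the objection stands in full.

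A reader might also picture the quote acting on that evening's dose. The protocol gives no dosing time and codes adherence per day, and a dose taken before 4 PM cannot respond to that day's quote. The simulations do not dilute for this, so they lean high.

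The strong scenarios are hard to square with the protocol's own account. It describes effects of dedicated static adherence interventions as small, and on every survey day, with or without a quote, AYAs receive a 6 PM survey that asks about 6-MP motivation. The extra cue from a quote may be slight. This stands too, and it keeps the point minor.

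The yardstick argument stands only in part. A detectable OR of 2.8 implies a standard error of ln(2.8) / 2.80 = 0.37. At that precision even the strongest scenario gives about 5.6% false positives. But that figure rests on an effective sample size of 59, whereas the within-person coefficient draws on up to 1890 person-days. Its simulated standard error of 0.066 corresponds to a detectable OR of exp(2.80 × 0.066) = 1.20.

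The aim is temporal association, and a later adherence intervention is meant to run beside engagement prompts, so an association averaged over prompts has some meaning. The article is also condensed, and an unseen analysis plan may add the term. Both are fair. Still, the article does list the model contents and covariate classes, and the one daily input that the study randomizes before the survey is not among them.

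**Conclusion.** The point holds as a minor one. The planned models omit a randomized, day-level study input that precedes AYA current-state ratings, and nothing else in the model can absorb it. Bias arises only if the quote affects both the rating and, by a separate route, that day's dose. Under modest assumed effects the inflation is negligible, at about 5% false positives. Under strong ones it is roughly 12% to 26%, with spurious odds ratios of about 1.05 to 1.09 in either direction. These rates rest on assumed quote effects, an intercept SD of 1.5 and a within-person standard error near 0.066.

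A reader might infer that the primary analysis is invalid or that every adherence model is exposed. The documents support neither. Caregivers receive no quotes, the 24-hour items mostly precede the quote, and calendar predictors cannot respond to it.

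**What to change.** In Primary Data Analyses, add the day's randomized quote assignment (1 = quote, 0 = nothing, as assigned) as a fixed effect in the adherence models whose predictor is an AYA-reported current-state item: affect, motivation, physical symptoms, loneliness, location or company. It is not needed for caregiver-reported, past-24-hour or calendar predictors.

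The cost is one sentence and one degree of freedom, and the app already generates the assignment. If the quote has no effect, the estimates stay essentially the same. One limit should be noted: predictors exist only on days with a completed survey, and the quote is meant to raise completion. The term therefore removes the common-cause path but does not deal with selection through completion, which belongs with the planned examination of missing data.

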An optimized JITAI is well suited to address the gaps in prior adherence-promotion interventions by maximizing engagement, minimizing burden, and delivering a personalized intervention only when there is a true benefit [35]. Consistent with the broader pediatric adherence-promotion literature [42,43], effect sizes from a few existing and static 6-MP adherence-promotion interventions are small and possess key limitations (eg, suboptimal participant engagement in digital health components and relying on parental supervision of medication taking, which may not be feasible or acceptable to an AYA population) [63,64]. Moreover, optimization questions regarding which intervention option to offer to AYAs and when have been neglected. The results from this EMA study will serve as an initial check of the time-varying contexts that are salient for 6-MP adherence, which will help inform the EMA questions that will be retained and used as tailoring variables in the JITAIs. Moreover, this study will help prescreen engagement components that will be further piloted in the intervention.

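### One-context-at-a-time models cannot show which survey items add information beyond the others, yet their significant findings help decide which questions are kept

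*Protocol article*

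**What the plan says.** Methods, Primary Data Analyses, fixes the model structure: "Separate mixed effects models will be constructed for different predictors". Each such model holds one context and a participant-level random intercept. On adjustment the section says: "Mixed effects models may also include demographic and treatment covariates". Other survey items are not named as covariates, and no model holding several contexts together is described. Each context is split into a person mean and a daily deviation from it ("We will decompose the between-subject and within-subject effects of EMA of contextual factors").

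The same section states the use: "Significant findings will inform tailoring variables for future JITAIs". Discussion, Overview, presents the results as a first look that will "serve as an initial check of the time-varying contexts that are salient for 6-MP adherence". It then names the decision that this look feeds: "which will help inform the EMA questions that will be retained and used as tailoring variables in the JITAIs".

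On the number of items, Study Design says: "Enrolled AYAs will complete 11 daily survey questions". Caregivers answer four.

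**The concern.** Choosing which questions to keep is a comparative task, and a one-predictor model does not compare items. It credits an item with the effect of everything that moves with it. The within/between split does not help, because both parts come from the same item.

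Overlap is likely. Table 1 shows pain, fatigue, nausea, positive and negative affect and loneliness as 0–4 ratings on the same survey. The article's own example shows the difficulty. The Introduction reports that in the pilot missed doses were more frequent on weekends and on days of worse motivation or negative affect, and Primary Data Analyses offers affect, motivation and day of week as possible tailoring variables. If all three replicate in separate models, the sponsor still does not know whether each adds anything to the other two.

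At stake is a later intervention that asks redundant questions, in a field where the article itself describes rapidly falling engagement.

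**Working it through.** **Inputs from the article.** 30 dyads × 63 days = 1890 person-days; 20% nonadherence; two-sided 0.05; within-subject correlation 0.5; 80% power at OR 2.8 per SD (Sample Size and Power). Survey completion 88.9% (pilot, Introduction) and 62.3% (original app trial, App Platform). Table 1 lists nine scored or yes/no AYA items plus location (9 options) and company (8 options).

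**Assumed, not in the article.** The within-person correlation ρ between items (0.3 to 0.7) and true odds ratios below 2.8.

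**The plan's own figure.** Effective n = 1890 / (1 + 62 × 0.5) = 1890/32 = 59.06, which reproduces the stated 59. The usual formula for one continuous predictor, ln(OR) = (1.960 + 0.842)/√(n·p(1−p)), with n = 59 and p = 0.20 gives OR 2.49. A 20% reduction in n gives 2.77, and a Wald-based formula gives 3.1 or more. The stated 2.8 lies within that spread. I do not call it an error, and nothing below rests on it.

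**Mechanism.** A proxy with no effect of its own, correlated ρ with the driver, shows roughly ρ × ln(OR) when tested alone. At OR 1.5 and ρ = 0.5 that is 0.5 × 0.405 = 0.203, an apparent OR of about 1.22 (simulated: about 1.23).

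**On the plan's power basis.** 80% power means a noncentrality of 2.80. The proxy's is ρ × 2.80, so at ρ = 0.5 its power is Φ(1.40 − 1.96) = 29%. The figures at ρ = 0.3, 0.7 and 0.8 are 13%, 50% and 61%.

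**In the day-level model.** Random-intercept logistic model with latent intercept variance 3.29 (ICC 0.5: 3.29/(3.29 + 3.29)), 20% misses, person-centred normal predictors, one driver and one proxy, 300 runs per cell. Simulation error is at most about ±1.96 × √(0.25/300) = ±6 points. Entries are the percentage significant, in the order ρ = 0.3 / 0.5 / 0.7 (at 62.3% completion, ρ = 0.3 / 0.5 only).

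| True OR | Completion | Proxy alone | Proxy, joint | Driver, joint |
|---|---|---|---|---|
| 1.3 | 88.9% | 17 / 38 / 70 | 6 / 5 / 4 | 90 / 89 / 69 |
| 1.5 | 88.9% | 36 / 75 / 93 | 4 / 6 / 5 | 100 / 100 / 98 |
| 2.8 | 88.9% | 95 / 100 / 100 | 6 / 6 / 3 | 100 / 100 / 100 |
| 1.3 | 62.3% | 14 / 31 | 3 / 4 | 79 / 70 |
| 1.5 | 62.3% | 24 / 60 | 5 / 6 | 99 / 97 |
| 2.8 | 62.3% | 85 / 100 | 10 / 5 | 100 / 100 |

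With ρ = 0 the proxy alone is significant in 2–4%. A variant with person intercepts (800 runs per setting, OR 1.5, both completion rates) gave 27–40%, 67–82% and 92–99% at ρ = 0.3, 0.5 and 0.7.

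**More items.** Two predictors flatter the joint model. With nine items (OR 1.3 to 1.5, ρ 0.3 to 0.7), a proxy alone was significant in 12–99%. The joint model held null items to about 4–6% each, with power for the true factor of 72–100% at OR 1.5 and 44–88% at OR 1.3.

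Dummy-coding location and company gives 9 + 8 + 7 = 24 terms. With assumed category frequencies (200 runs per cell), power at ρ = 0.5 / 0.7 was:
- OR 1.5: 95% / 85% at 88.9% completion and 86% / 72% at 62.3%.
- OR 1.3: 73% / 54% at 88.9% completion and 53% / 41% at 62.3%.

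At least one of the eight null scored items was still significant in 27–38% of runs.

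**Events.** 0.20 × 1890 = 378 misses at most, and 0.623 × 378 ≈ 235 at the lower completion. For a model needing both surveys, independent completion at 62.3% leaves 0.623² = 39% of days. Power was then 46–72% at OR 1.5 and 27–41% at OR 1.3.

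**The case against.** The plan has a good defence. The stated aim is temporal association, and single-item models estimate exactly that. The Introduction defines a tailoring variable as information used to make decisions, so a reliable marker of a risky day can serve without being the cause. Significance is not the sole rule: findings inform the choice, and under Future Directions a multidisciplinary team with patient representatives selects tailoring variables using theory and other evidence. In a preparatory screen, losing a useful item may cost more than carrying a redundant one forward. All of this stands, and it keeps the single-item models primary.

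A reader might infer three stronger things that the article does not support.

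- That proxies will usually pass the screen. This needs a correlation the article never gives. At OR 1.3 with ρ of 0.3 to 0.5 the two-predictor rate is 14–38%, and on the plan's power basis it reaches one half only at ρ of about 0.7.
- That the study cannot separate the items. All are collected on the same days, and a joint model separated driver from proxy in simulation.
- That single-item results fail the hypothesis. The Objectives claim no independent effect for each factor, and a joint model of observational ratings would not establish causation either.

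The separate analysis plan is not shown and may already contain a joint model. What remains is that the analysis described does not show which items carry information the others lack, although the results are meant to guide which questions are kept.

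**Conclusion.** The point holds as a cheap improvement, not as a failure of the primary analysis. The described models cannot show which items add information beyond the rest; the planned data can, within limits of power. For true odds ratios of 1.3 to 1.5 and within-person correlations of 0.3 to 0.7, a pure proxy is significant in roughly 12% to 99% of simulated studies. At the design odds ratio of 2.8, with ρ of 0.3 or more, the day-level figure is 85–100%. These figures assume the stated correlations, normal scores and no serial dependence. Real 0–4 items, with more of them correlated, would separate less cleanly. A joint model as the only retention rule is not supported, because it could discard true factors of modest size.

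**What to change.** Keep the single-predictor models as primary and label their results total associations, since motivation may mediate mood. Add two prespecified supportive mixed models using within-person deviations:

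1. All scored AYA items together, or by domain, with location and company collapsed to a few categories (for example home versus not, with caregiver versus not).
2. The same model plus the caregiver items, on days with both surveys.

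Report both sets of estimates with intervals and use them together when deciding which questions to retain. State that no item is dropped on joint-model non-significance alone.

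The cost is two extra models and a few sentences, with no new data or participant burden. The downsides are wider intervals and lower power for strongly correlated items, and fewer usable days in the caregiver model.

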## Introduction

### Background

For patients with acute lymphoblastic leukemia or lymphoma, durable cancer remission requires a prolonged maintenance phase characterized by 18-30 months of a regimen that includes daily oral intake of the chemotherapy agent 6-mercaptopurine (6-MP) [1,2]. In a trial conducted by the Children’s Oncology Group, nearly 50% of children and adolescents demonstrated electronically monitored 6-MP adherence rates below a 95% critical level for relapse prevention, resulting in a 2.5 times greater risk for relapse in nonadherent patients [1]. In this study and others, adolescents and young adults (AYAs) with cancer demonstrated lower oral chemotherapy adherence than their younger counterparts [2-6]. AYA treatment adherence is often at odds with normative developmental goals, such as establishing autonomy and navigating social pressures, as well as neurodevelopmental changes that occur during these years (eg, developing executive functions) [7-9]. Although cross-sectional studies have begun to identify contextual risk factors for oral chemotherapy nonadherence, including physical symptoms [10,11], negative mood [10,12], low motivation [13,14], difficult family interactions [15-17], and environmental factors (eg, being outside of the home) [15,17,18], these multifactorial and dynamic contexts can vary from day to day within individuals [19]. It remains unclear how these idiosyncratic factors affect daily 6-MP adherence, complicating the development of personalized mobile health (mHealth) interventions to deliver effective, contextualized, and timely adherence support [20-23]. For addressing this gap, this paper describes the protocol for an app-based ecological momentary assessment (EMA) study of AYAs with cancer.

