### Sample Size and Power

Power calculations were performed using the PASS 2021 [59]. With 63 days of repeated measures and assuming a moderate within-subject correlation of 0.5, the most effective sample size for predicting our binary adherence outcome (took dose vs not) is 59 AYAs [60]. However, our study sample size is constrained by the available AYAs who meet the inclusion criteria at our single institution. With our proposed sample size of 30 AYA-caregiver dyads, assuming a two-sided type 1 error of 0.05 and an approximate nonadherence rate of 20% (based on estimates from prior studies) [28,61], we will have 80% power to detect an odds ratio of 2.8 (a large effect) for every 1 SD increase in a continuous predictor [62].

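### With only a random intercept, the standard error of the average within-person effect is too small if AYAs differ in how their adherence responds to a factor

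*Protocol article*

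**What the plan says.** Primary Data Analyses names SAS PROC GLIMMIX for the binary daily 6-MP outcome and states the structure: "Separate mixed effects models will be constructed for different predictors", and these "include the predictor as the fixed effect and a random intercept for each participant to account for between-person variability". Each contextual score is split into a person mean and a daily departure from that mean, so the coefficient of the departure is the test of the primary hypothesis in Objectives. No random slope or empirical standard error is mentioned.

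The use of the results is also stated: "Significant findings will inform tailoring variables for future JITAIs". The type 1 error level comes from Sample Size and Power, "assuming a two-sided type 1 error of 0.05 and an approximate nonadherence rate of 20" percent. Background gives the motivation: "It remains unclear how these idiosyncratic factors affect daily 6-MP adherence".

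**The concern.** A random intercept lets AYAs differ in their average adherence. It does not let them differ in how adherence moves with mood, symptoms or family conflict. The model treats the slope as common to all 30 AYAs, so the large number of days makes that slope look precisely estimated. If slopes differ, the average slope is learned from 30 people, and its uncertainty has a between-person part that more days per person cannot remove.

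The study needs inference about AYAs beyond these 30, because the results feed later interventions. At stake are the error rate of the primary tests and the width of their intervals. A factor with no average effect, but with differing effects across individuals, would too often appear to have an average effect in one direction.

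**Working it through.** **Inputs from the protocol.** "30 AYA-caregiver dyads×63 days=a maximum of 1890 daily observations" (Primary Data Analyses); "an approximate nonadherence rate of 20" percent, two-sided 0.05, and "assuming a moderate within-subject correlation of 0.5" (Sample Size and Power).

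**Assumed input.** The between-person SD of the within-person slope, τ, in log-odds per within-person SD. The documents give no value; the range used is 0 to 0.7.

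**The plan's own figures.** The effective sample size reproduces: 1890 / (1 + 62 × 0.5) = 1890 / 32 = 59.06, stated as 59. The detectable odds ratio of 2.8 was not reproduced. The Hsieh formula, (ln OR)² = (1.960 + 0.842)² / [59.06 × 0.2 × 0.8], gives OR 2.49, and other standard variants give 2.51 to 3.50. An unstated R² of about 0.2 in the Hsieh formula would give about 2.8. The article does not name the routine used, and nothing below depends on this figure.

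**Analytic check.** With 30 participants, the variance of the average slope gains about τ²/30, which the random-intercept model omits. So

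true SD / reported SE ≈ √(1 + τ² / (30 × SE²)), and rejection rate = 2 × [1 − Φ(1.96 / ratio)].

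Example with SE 0.062 and τ = 0.3: 0.09/30 = 0.0030; 0.062² = 0.003844; ratio = √1.780 = 1.33; 1.96/1.33 = 1.47; rejection 14.2%.

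**Simulations with zero average effect.**

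- Simulation 1: 600 replicates, with 88.9% survey completion (the pilot mean in Background), random-intercept logit by Gauss-Hermite quadrature.
- Simulation 2: all 63 days observed, normal predictor without autocorrelation, independent slope and intercept. The intercept SD is 1.0 or 1.814; the latter is √(π²/3), a latent-scale correlation of 0.5. About 600 runs per cell by pseudo-likelihood (at most 2 diverged runs dropped) and 200 by quadrature.

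Rejection rates (%) at nominal 5%. Pairs are intercept SD 1.0 / 1.814 for simulation 2, and SE 0.062 / 0.070 for the formula:

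| Slope SD | Sim 1 | Sim 2, pseudo-likelihood | Sim 2, quadrature | Formula |
|---|---|---|---|---|
| 0 | 4.8 | 4.0 / 4.0 | 3.0 / 5.5 | 5.0 / 5.0 |
| 0.1 | not run | not run | not run | 6.0 / 5.8 |
| 0.2 | not run | 8.7 / 8.3 | 8.0 / 8.0 | 9.1 / 8.2 |
| 0.3 | 15.3 | 14.0 / 13.2 | 12.5 / 13.0 | 14.2 / 12.3 |
| 0.5 | 25.5 | 27.2 / 26.6 | 28.0 / 24.5 | 27.1 / 23.3 |
| 0.7 | 36.2 | 38.5 / 37.8 | 39.0 / 36.5 | 39.2 / 34.6 |

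Monte Carlo error at 600 runs is about 0.9 points near 5% and 2 points near 38%.

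In simulation 1 the empirical SD against the mean reported SE was 0.073/0.075, 0.097/0.074, 0.124/0.074 and 0.150/0.073 at slope SD 0, 0.3, 0.5 and 0.7, that is ratios of 0.97, 1.31, 1.68 and 2.05.

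**Remedies on the same data.** At slope SD 0.2 to 0.7 in simulation 2, the random-slope model rejected 3.7 to 5.0% and the participant-clustered SE 3.8 to 5.0%, both on t with 29 df. At slope SD 0 they rejected 2.2 to 2.8% and 4.0 to 5.3%. In simulation 1 the clustered SE rejected 4.5 to 5.8% across all scenarios.

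**The case against.** The strongest reply is that the quantity driving the size is not in the documents. This stands: inflation is slight at slope SD 0.1, modest at 0.2, and large only from about 0.3 upward. An SD of 0.3 around zero means that 95% of individual odds ratios lie between exp(−0.588) = 0.56 and exp(0.588) = 1.80. At 0.7 the span is 0.25 to 3.94, with half of the AYAs responding in each direction, which is a strong assumption for pain or low motivation.

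A reader might infer from Background that the protocol itself posits differing slopes. It does not. The adjective there describes the factors, after a sentence on contexts varying within individuals, and the hypothesis in Objectives is a common direction of effect. The personalization aim makes differing slopes plausible and no more.

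A reader might also infer that significance alone selects tailoring variables. The article says that findings inform the choice, and Future Directions leaves the initial set to a multidisciplinary team with AYA representatives, who also draw on theory and other evidence.

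A third tempting step is to multiply the inflated rate by 15 survey items (11 for AYAs, 4 for caregivers). That count is loose: location and company are multi-category, disagreement is yes/no, and dyadic predictors are added. Multiplicity is a separate matter that a SAP could settle, and this point does not need it.

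It can also be said that a factor acting on individuals in opposite directions is a fair candidate for tailoring, and that a factor affecting nobody is tested at about 5%. Both are true. But the planned model would report such a factor as an average effect in one direction and would not estimate the variation that matters for tailoring.

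Finally, the article is condensed and does not expressly exclude random slopes. Still, it writes out the random-effects structure, and its natural reading is an intercept alone.

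**Conclusion.** The point holds as a conditional one. As written, the model gives valid standard errors for the average within-person effect only if AYAs share nearly the same slope. At a zero average effect, the nominal 5% test rejects about 5%, 6%, 8 to 9%, 13 to 15%, 25 to 27% and 36 to 38% at slope SD 0, 0.1, 0.2, 0.3, 0.5 and 0.7. Coverage of the nominal 95% interval there is 100% minus these figures, for example 85 to 87% at SD 0.3.

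The figures assume 30 AYAs, 20% missed doses and a slope SD that the documents do not supply; missed surveys reduce the inflation somewhat. The documents do not support saying that the study's actual false-positive rate is well above 5%. They support saying that the stated model gives no protection if slopes vary, in a study whose purpose makes variation plausible.

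**What to change.** Before the primary models are run, add a random slope for the within-person predictor. Where it does not converge, keep the random intercept and use a participant-clustered empirical (sandwich) standard error with a small-sample correction and about 29 degrees of freedom. Report the estimated slope SD for each factor, since it bears directly on personalization.

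This is a small change of code per model and needs no new data. The cost is wider intervals when slopes vary. Taking exp[(1.96 + 0.84) × SD of the estimate] from simulation 1, the detectable odds ratio per within-person SD at 80% power is exp(2.8 × 0.097) = 1.31 at slope SD 0.3, exp(2.8 × 0.124) = 1.42 at 0.5 and exp(2.8 × 0.150) = 1.52 at 0.7, against about 1.23 with homogeneous slopes. All are well below the odds ratio of 2.8 that the plan accepts. If slopes are homogeneous little is lost, although the random-slope test is then somewhat conservative.
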